##### Recruitment and randomisation

For the selection of GPs, the research project will rely on pre-selected primary care centres. Twenty GPs will be selected by using a non-probabilistic consecutive sampling method: 10 GPs as the control group and 10 GPs as the study group. To do that, GPs will be invited to participate and will be included in either group by using a block randomisation technique. Each block is formed by four GPs among whom the two study arms will be uniformly distributed. Once the blocks have been created, they will be distributed using a sequence of random numbers and the final list of GP allocations will be created. The final list of GP allocations will be guarded by the principal investigator of the project, and he will inform the allocation of each GP included in the trial.

The GP’s inclusion visit will be carried out once the randomisation has been done. In this visit, all of the study’s variables are collected and the inhalation technique of each inhaler is evaluated through a specific step-by-step test. This test was specially designed for this study on basis of the Sociedad Española de Neumología y Cirugía Torácica (SEPAR) recommendations [4] for most of the commonly used devices (Spiriva HandiHaler, Boehringer Ingelheim, Ridgefield, CT, USA; Seretide Accuhaler, GlaxoSmithKline, Philadelphia, PA, USA; turbuhalers; pressurized metered-dose inhalers; and Breezhaler, Novartis, Basel, Switzerland).

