### Study aims

Our research group has studied the management of chronic illness in primary care for more than 15 years, focusing mainly on COPD. The first step taken was to carry out trials to develop tools to assess therapeutic adherence and educational interventions to improve adherence. Our first educational intervention was designed with three components (motivational and cognitive aspects, as well as skill development in inhalation techniques). The intervention was evaluated in a randomised controlled trial which showed that treatment adherence improved by 48 % (relative risk) with a number needed to treat (NNT) of 6.37 [14]. In the last 3 years, our clinical trials have been focused on the evaluation of educational interventions to improve inhalation techniques in patients with COPD. We have designed two educational interventions to improve inhalation technique: (1) only written information (leaflet) or (2) written information (leaflet) reinforced by instructor training. These trials showed that an intervention with a demonstration by a trainer is significantly more effective than an informative leaflet alone, with an increase in the number of patients who develop proper inhalation technique by 48 % at 3 months and by 41 % at 1-year follow-up [21].

The next step is the start-up of an intervention focused on primary health care professionals so that they are well-trained. The main goal is to evaluate the efficacy of an educational intervention to train general practitioners (GPs) in the right inhalation technique for the most commonly used inhalers and, afterwards, to evaluate the improvements in inhalation techniques performed by their patients. The secondary outcomes of this intervention will be a clinical control improvement and follow-up of the disease as well as improvement in health-related quality of life. All of these outcomes have been key goals for more than 10 years.

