##### Interventions in GPs

The intervention consists of a demonstration of correct inhalation technique and the rationale for it to a group of two to four GPs. After the demonstration, the participants are asked to identify their mistakes and ask any questions they may have, which will be resolved until full understanding of the technique is achieved. The intervention will take approximately 15 minutes to deliver. Reinforcement with written information is provided via the patient’s data collection form (DCF), where the specific step-by-step schedule for each device is recorded at each patient’s visit (initial visit and at 3 and 6 months).

Blinding of the intervention for GPs will not be possible for either researchers or GPs. Table 1 provides a brief summary of the interventions for the first- and second-level participants.

**Table 1 Tab1:** Brief summary of interventions in first and second levels

	Second level: professionals (GPs)	First level: patients
Content	Inhalation technique workshop:	Inhalation technique workshop:
	• Step-by-step correct technique demonstration (how)	• Step-by-step correct technique demonstration (how)
	• Explanation of each step for each device (why)	• Explanation of each step for each device (why)
Who applies the intervention	Research team	GPs from the intervention group
Who receives the intervention	GPs from the intervention group	Patients with COPD from the intervention group

*COPD* chronic obstructive pulmonary disease, *GP* general practitioner

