#### Group variables/second-level variables (GPs)

Group and second-level variables are correct performance of the inhalation techniques by GPs (evaluated using a specific step-by-step test for each inhaler, described below), knowledge about COPD and its treatment (evaluated by using a questionnaire specially designed for this study and based on COPD PAI [16], Spanish COPD Guidelines [15] and GOLD guidelines [2]).

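### The GPs' own baseline technique and knowledge are measured after randomisation, and nothing keeps allocation undisclosed until the test is done

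*Protocol article*

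**What the plan says.** Under Recruitment and randomisation, the protocol article describes block randomisation of 20 GPs, 10 per arm, in blocks of four. The principal investigator holds the allocation list, and "he will inform the allocation of each GP included in the trial". The next paragraph says that the GP's "inclusion visit will be carried out once the randomisation has been done". At that visit all the study's "variables are collected and the inhalation technique of each inhaler is evaluated through a specific step-by-step test".

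The section on second-level variables shows what this covers: "correct performance of the inhalation techniques by GPs", and "knowledge about COPD and its treatment (evaluated by using a questionnaire specially designed for this study". The GP Follow-up section has the same variables and the technique evaluation repeated at 1 year.

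On masking, the section Interventions in GPs states: "Blinding of the intervention for GPs will not be possible for either researchers or GPs". Table 1 in that section has the research team delivering the training.

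The Study aims section places GP training inside the principal objective: "The main goal is to evaluate the efficacy of an educational intervention to train general practitioners (GPs"). Patients' technique is to be evaluated afterwards.

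**The concern.** A baseline value is useful because allocation cannot have affected it. Here the order of events does not guarantee that. Both GP measures can respond to knowing the arm. A technique test can be rehearsed, or done with little effort by someone who expects to be taught. A knowledge questionnaire can be prepared for. A checklist scored by an observer can be marked differently if the observer knows the arm.

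The GP training effect is at stake. It is part of the main goal and the route by which patients are meant to benefit. If it is judged by change from the inclusion visit to 1 year, or adjusted for the inclusion-visit result, any influence of allocation on the first measurement passes into the estimate. Comparing the arms at baseline would not show cleanly whether randomisation had balanced GP technique. There is also a gap in the data: a GP who withdraws between randomisation and the inclusion visit is a randomised cluster with no baseline.

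**Working it through.** The protocol gives no figure on this point to reproduce, so the check is of sequence and masking.

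1. **Order.** Recruitment and randomisation puts the GP inclusion visit after randomisation. This is explicit.

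2. **Content of the visit.** All study variables plus the technique test for each inhaler. The second-level variables are GP technique and COPD knowledge, so both baselines follow randomisation.

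3. **Disclosure.** The principal investigator tells GPs their allocation. The article does not say whether this comes before or after the inclusion visit, or where the 15-minute training falls relative to it. No step withholds allocation until the test is finished.

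4. **Masking of the GP assessment.** Masked data collection appears in three places, and each concerns patients:
   - Follow-up under first-level participants: a research assistant unaware of GP randomisation.
   - Interventions in patients: an external researcher collecting patient data.
   - Study limitations: the external researcher at the patient inclusion visit and visit 1.

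   No masked assessor is described for the GP tests. The only masking statement in the GP sections says that blinding to the intervention is not possible.

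5. **Loss after randomisation.** The GP exclusion criteria include having to leave the job during the trial. With baseline taken after randomisation, a GP lost early may have no baseline record.

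6. **What depends on the baseline.** A change score, a baseline-adjusted estimate and a between-arm baseline comparison of GP technique or knowledge all use it. A comparison of the randomised arms at 1 year does not. The patient primary outcome is measured on patients by a masked assistant and does not use it either.

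7. **Could the data reveal the problem?** As an illustration only, assume that each GP's result is reduced to correct or incorrect, with true proportion p in both arms. The standard error of the baseline difference with 10 GPs per arm is √(2p(1−p)/10).
   - p = 0.2: √(2 × 0.2 × 0.8/10) = √0.032 = 0.179.
   - p = 0.5: √(2 × 0.5 × 0.5/10) = √0.05 = 0.224.

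   Chance alone gives a standard error of about 18 to 22 percentage points, so a moderate shift caused by allocation could not be told from chance imbalance. This is not an estimate of bias. It shows why the safeguard has to be in the procedure.

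**The case against.** The strongest reply is that much of the harm rests on things the article does not state.

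- **Disclosure before testing.** A reader might infer that GPs are told their arm and tested only afterwards. The text does not say so; randomising first and disclosing after the visit would also fit it. What stands is that the order is left open and no safeguard is given.
- **Unmasked scoring.** A reader might infer that the GP test is scored by someone who knows the arm. The blinding sentence concerns the intervention, and the GP assessor is never named. What stands is that masking is described for patient data only.
- **Control GPs' motivation.** The Study limitations section worries that control GPs may be less motivated, and this might be read as admitting a distorted baseline. It concerns differing recruitment between arms, not GP test results, and lends no support here.
- **A size for the bias.** With 10 GPs per arm it is tempting to let each altered result count for 10 percentage points. That presumes one yes/no result per GP. The protocol tests each of several inhalers and adds a questionnaire, and it states the all-steps-correct rule only for patients.
- **No baseline-dependent GP analysis is specified.** This is correct. The listed primary and secondary outcomes are patient outcomes, and a 1-year comparison of GP arms is randomised without any baseline. It limits the point but does not remove it: GP variables are collected twice and GP training is in the main goal, so use of the baseline is foreseeable.

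**Conclusion.** The point holds in a limited form. The GP baseline is scheduled after randomisation, GPs and researchers cannot be blinded to the GP intervention, and nothing keeps allocation undisclosed until the baseline is recorded. The baseline can therefore be influenced by allocation, and it may be missing for GPs who withdraw early. Any change-from-baseline or baseline-adjusted account of the GP training effect is weakened accordingly.

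No size or direction can be given. The conclusion assumes that allocation may be known to the GP or the tester at the inclusion visit, which the text permits but does not state. A reader might conclude that the trial's main result is biased; the document does not support that, because the primary outcome is a patient measure with a masked assessor. The 1-year comparison of GPs between arms is also free of this particular problem, although no masked assessor is described for that visit either.

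**What to change.** For GPs still to be recruited in the second phase (Trial status), complete the technique test and knowledge questionnaire after consent and before allocation is generated or disclosed. Because the principal investigator already holds the list, it is enough to release each GP's allocation only once that GP's baseline form is complete, provided that the person running the test has not seen the list. State this order in the protocol.

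For GPs already tested after randomisation, report this as a limitation. Base the GP-level training effect on the between-arm comparison at 1 year, and treat change from baseline as descriptive.

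The cost is small: existing steps are reordered and no data are added. The drawback is that baseline timing will differ between the two recruitment phases, which should be stated when GP baselines are reported.

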##### Follow-up

Both groups of GPs will be followed up 1 year after the inclusion visit. In this visit (visit 1), all variables will be collected once again, and the GPs use of the inhalation technique will be evaluated.

##### Interventions in GPs

The intervention consists of a demonstration of correct inhalation technique and the rationale for it to a group of two to four GPs. After the demonstration, the participants are asked to identify their mistakes and ask any questions they may have, which will be resolved until full understanding of the technique is achieved. The intervention will take approximately 15 minutes to deliver. Reinforcement with written information is provided via the patient’s data collection form (DCF), where the specific step-by-step schedule for each device is recorded at each patient’s visit (initial visit and at 3 and 6 months).

Blinding of the intervention for GPs will not be possible for either researchers or GPs. Table 1 provides a brief summary of the interventions for the first- and second-level participants.

**Table 1 Tab1:** Brief summary of interventions in first and second levels

	Second level: professionals (GPs)	First level: patients
Content	Inhalation technique workshop:	Inhalation technique workshop:
	• Step-by-step correct technique demonstration (how)	• Step-by-step correct technique demonstration (how)
	• Explanation of each step for each device (why)	• Explanation of each step for each device (why)
Who applies the intervention	Research team	GPs from the intervention group
Who receives the intervention	GPs from the intervention group	Patients with COPD from the intervention group

*COPD* chronic obstructive pulmonary disease, *GP* general practitioner

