##### Follow-up

The follow-up of patients will be limited to 1 year after the inclusion visit by the research team. During the inclusion visit, all variables will be measured again, including the evaluation of inhalation techniques. All measurements will be taken by a research assistant who has no knowledge of either the randomisation of the GPs or whether the patients belong to the study or control arm.

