##### Interventions in patients

The patients included in the intervention group will receive an educational intervention from their GPs, who will train them in the correct use of their devices. This intervention will consist of the following:Performance of inhalation techniques to detect mistakes that will be registered on a specially designed sheetDemonstration of proper inhalation techniquesIdentification of mistakes in technique and opportunities to ask health professionals about how to perform inhalation properly

The patients will be given an appointment for reinforcement visits at 3 and 6 months after the inclusion visit. In these visits, the GPs will encourage and refresh their performance of inhalation techniques.

As the educational intervention will not be blinded, the external researcher responsible for collection of patient data will not know the patient allocation. The patients included in the control group will follow the standard clinical practice.

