### Study limitations

The first limitation is about the actual study design. In pragmatic cluster randomised controlled trials, the first bias to take into account is the selection bias, as the randomisation is usually applied in the second level, before recruitment of the first-level participants, which is where the intervention impact is measured. However, there are strategies that minimise this bias, and we are using these in this study. First, the selection and follow-up of patients (patient inclusion visit and visit 1) will be carried out by an external researcher who will have no knowledge of GP randomisation. Second, the effect of the intervention over recruitment can lead to different recruitment indexes, depending on the groups, due to the possibility that GPs in the control group could be less motivated to participate. Moreover, to avoid different recruitment indexes in both groups, once the trial is finished, the GPs in the control group will be trained in the same way as the study group professionals were trained (if the intervention shows a significant improvement in patients) [23, 32].

Another study limitation is the potential for loss to follow-up. To minimise these losses, patients will be contacted at least three different times and at different times of day. However, loss to follow-up was taken into account in the sample size calculation and will be taken into account in performing data analysis (intention-to-treat analysis).

Another bias is the Hawthorne effect, which relates to how participants in a study change their behaviour under observation. However, we believe that the effect of this bias will be minimal because of patients’ being trained and followed by their GPs, with the exception of the inclusion and final visits. Besides, there is a control group in which the follow-up will permit us to minimise the real impact of this bias.

There could be measurement bias due to mistakes in recording of some variables or interviewer bias due to the administration of the questionnaires. To minimise these biases, interviewers will have been trained previously to ensure that visits will be as homogeneous as possible. A DCF and a manual that explains how each variable is measured at the follow-up visits will be given to the GPs in the intervention group.

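### No masked scorer is named for the GPs' 1-year inhaler-technique test, although masked assessment is arranged for patients, so the GP-level result is open to observer bias.

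*Protocol article*

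**What the plan says.** All references are to the protocol article.

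- **Interventions in GPs:** "Blinding of the intervention for GPs will not be possible for either researchers or GPs". Table 1 in the same section gives the research team as the party that trains the GPs in the intervention group. Training is given to groups of two to four GPs.
- **Recruitment and randomisation (GPs):** "The GP’s inclusion visit will be carried out once the randomisation has been done". GP technique is first tested at that visit, with a test made for this study.
- **Follow-up (GPs):** one year later, in both arms, "all variables will be collected once again, and the GPs use of the inhalation technique will be evaluated". No scorer is named and masking is not mentioned.
- **Group variables/second-level variables (GPs):** the measure is "correct performance of the inhalation techniques by GPs (evaluated using a specific step-by-step test for each inhaler".
- **Follow-up (patients):** "All measurements will be taken by a research assistant who has no knowledge of either the randomisation of the GPs", nor of the patients' arm.
- **Interventions in patients:** the education is not blinded, yet "the external researcher responsible for collection of patient data will not know the patient allocation".
- **Study limitations:** selection and follow-up of patients "will be carried out by an external researcher who will have no knowledge of GP randomisation".
- **Study aims:** the main goal covers training GPs in correct technique and then the improvement in their patients' technique.

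**The concern.** A step-by-step technique test depends on an observer's judgement of each step. A scorer who knows which GPs attended the workshop may credit borderline steps more readily in that group. The GP baseline visit also follows randomisation, so the allocation already exists whenever a GP is scored.

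Two things are at stake. First, whether training improved the GPs' own technique is part of the main goal. Second, GP technique is the step through which patients are meant to benefit. If patients did not improve, an inflated GP result would wrongly suggest that the training worked but was not passed on.

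**Working it through.** **Textual check.** The plan gives no figure to reproduce on this point, so the main check sets the sections side by side.

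| Question | Patients | GPs |
|---|---|---|
| Can the intervention be masked? | No (Interventions in patients) | No (Interventions in GPs) |
| Who delivers it? | GPs of the intervention group (Table 1) | Research team (Table 1) |
| How is technique measured? | Step-by-step test | Step-by-step test |
| Is a masked assessor named? | Yes, in three sections | No, in none |

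The section on interventions in patients accepts that an unblinded intervention is compatible with a data collector who does not know the allocation. The same reasoning applies to GPs, because the session scored at 1 year is separate from the workshop. The article nevertheless stops at the statement that masking is not possible.

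**Illustration of size.** The article gives no number of steps, no expected accuracy and no GP pass rule, so every input below except the 10 versus 10 GPs (Recruitment and randomisation) is assumed. The all-steps-correct rule is stated for patients only and is borrowed here.

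*Model 1, leniency per step.* With k independent steps, each correct with probability s, the pass rate is s^k. If the scorer raises s by d in the trained arm and there is no true effect, the spurious gain is (s + d)^k − s^k.

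- k = 10, s = 0.95, d = 0.02: 0.97^10 − 0.95^10 = 0.737 − 0.599 = 0.139, or 14 points.
- k = 10, s = 0.90, d = 0.02: 0.92^10 − 0.90^10 = 0.434 − 0.349 = 0.086, or 9 points.
- Over k = 8 to 12, s = 0.90 to 0.95 and d = 0.01 to 0.02: from 4 points (k = 8, s = 0.90, d = 0.01) to 15 points (k = 12, s = 0.95, d = 0.02).

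For 10 trained GPs, 14 points is 10 × 0.14 = 1.4 GPs. By exact enumeration at 10 versus 10, the two-sided 5 % chi-square rejection rate rises from 4.0 % to 8.0 % in the first case and from 3.9 % to 5.5 % in the second. Fisher's test gives 3.2 % and 1.9 %.

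*Model 2, leniency per GP.* The true pass rate is p, and the scorer passes a share L of the trained GPs who truly fail. The spurious gain is (1 − p) × L.

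| True pass rate p | Gain, L = 0.10 | Chi-square rejection | Gain, L = 0.30 | Chi-square rejection |
|---|---|---|---|---|
| 15 % | 8.5 points | 4.7 % | 25.5 points | 20.3 % |
| 30 % | 7 points | 4.8 % | 21 points | 13.7 % |
| 50 % | 5 points | 4.7 % | 15 points | 8.8 % |

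Without leniency the rejection rates are 2.1 %, 3.7 % and 4.2 %. In both models the estimate is biased upward whenever leniency is present. Significance is clearly affected only when leniency is strong.

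**The case against.** The strongest reply has four parts.

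1. **The masking statement concerns the intervention, not the assessment.** This is right as a literal reading. A reader might infer that the protocol declares the GP scorer unmasked; no sentence says so. What stands is that this is the only masking statement at GP level, that it names researchers, and that no section on the GP test adds a masked scorer. An article may leave such detail to the full protocol, but this one states masked assessment repeatedly, and only for patients. The reference to all measurements in the patient Follow-up section does not fill the gap, since it stands under the patient heading.
2. **GP technique is not a designated outcome.** This is also right. It is listed as a second-level variable. The hypothesis and sample size concern patients, and no between-arm test of GP technique is explicitly specified. A reader might call it the endpoint of a GP-level comparison, or half of the main goal; the article supports only that it is part of that goal.
3. **The result that decides the trial is protected.** Patient technique has an assessor unaware of allocation, and leniency in scoring GPs cannot alter it.
4. **Using the patient assessor for GPs could harm patient-level masking.** The 20 GPs share 8 centres, training is in small groups, and recruitment runs in two phases. A GP who reveals the arm could expose colleagues whose patients are still to be assessed, so waiting only for that GP's own patients is not enough. Waiting may also carry the GP test past 1 year. Both points stand and shape the fix.

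**Conclusion.** The point holds in a limited form. The article treats masking at GP level as impossible for researchers, which is true of delivering the workshop but not of scoring the test a year later, and it arranges no masked scorer for that test. The GP-level technique result is therefore open to observer bias.

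The size cannot be established from the article. The 4 to 15 points of the per-step model and the 5 to 25.5 points of the per-GP model show only what is possible under assumed steps, accuracy, independence and leniency, with a pass rule stated for patients alone. A reader might infer that leniency would produce a false significant training effect. The calculations do not support that in general: at 10 versus 10 GPs, rejection stays near 5 % under mild leniency and rises materially only under strong leniency.

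Nothing here touches the primary outcome or the sample size. It is a low-cost design improvement that is worth making.

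**What to change.** In the GP sections on follow-up and interventions:

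- Limit the statement that masking is impossible to delivery of the workshop.
- Have the 1-year GP technique test scored by an existing team member who did not deliver the workshop and is not told the allocation.
- Allow the masked patient assessor to do this only after completing the final patient visits at that centre, and record the date of each GP test.
- Ask GPs not to mention training before the test is scored, and record any unmasking.
- If no masked scorer can be arranged, report the GP-level result as assessed without masking.

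The cost is a change of wording and the scheduling of 20 GP tests. If the patient assessor is used, some GP tests may fall later than 1 year. A residual risk that a GP reveals the arm remains under any arrangement.
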